## Methods

### Study design

In this multicentre observational cohort study, patients clinically diagnosed with subacromial impingement syndrome in either one of 3 participating hospitals (Leiden University Medical Centre (LUMC), Medical Centre Haaglanden (MCH), Rijnland Hospital Leiderdorp) will be included for analyses at the LUMC Laboratory for Kinematics and Neuromechanics.

The Medical Ethics Committee of the university medical centre approved all stages of the study. Written informed consent will be obtained from all patients.

### Study population

#### Selection of participants

Patients will be recruited by 3 orthopaedic surgeons involved in the 3 participating hospitals. Patients will be selected if one or more of the following (limited) usual care criteria are present, next to a positive Neer impingement test (lidocaine) and a positive Hawkins test:

Patients' history:

◦ diffuse unilateral shoulder pain for > 3 months;

◦ pain during activities with abduction, retroflexion and/or internal rotation (e.g. closing the door, putting on jacket, overhead activities);

◦ pain at night or incapable of lying on the shoulder.

Physical examination:

◦ positive Yocum test;

◦ painful arc;

◦ diffuse pain at palpation of the greater tuberosity;

◦ disturbed scapulohumeral rhythm;

◦ no signs of pathologies or symptoms on the controlateral shoulder;

◦ capable of 90 degrees of passive abduction and 90 degrees of external rotation.

After the first and clinical inclusion round, symptoms of eligible patients are further investigated with the use of standard shoulder radiographs (anteroposterior in both external and internal rotation and Y scapular view (scapular outlet view)) and an MRI-arthrography of the shoulder. The MRI-arthrographies are evaluated at the local hospital for clinical purposes and additionally evaluated by one of two participating musculoskeletal radiologists at LUMC for eligibility criteria and assessment of acromion classification and rotator cuff status.

Patients are excluded if one of the following characteristics is found with the visit to the outpatient clinic, standard shoulder radiographs or MRI-arthrography:

◦ Age below 35 years or above 60 years;

◦ Restrictions in passive movements of the glenohumeral joint (adhesive capsulitis);

◦ History of fracture or dislocation of the shoulder, history of surgery around the shoulder;

◦ Co-morbidities on the affected shoulder (including fractures, benign or malignant tumours, labrum abnormalities, Hill Sachs lesion, capsular or ligamentous abnormalities, glenohumeral instability, glenohumeral movement restriction, glenohumeral or symptomatic acromioclavicular osteoarthritis, rheumatic disorder, biceps muscle tendinitis, complete (full thickness) rotator cuff rupture, cervical radiculopathy, PASTA lesion, Pulley lesion, calcifying tendinitis > 3 mm, or neurological deficits);

◦ Symptoms on the controlateral shoulder;

◦ No informed consent.

Patients with either rotator cuff tears or calcifying tendinitis are included, if eligible, in separate research projects.

#### Sample size

A combination of techniques will be applied to classify SIS-patients into pathophysiologic subgroups, most of which are newly developed (section 2.3). The acromiohumeral distance (AH) is a recognized parameter related to rotator cuff disease and based on literature it has rather wide inter-individual variations. Therefore, sample size calculation will be based on this parameter.

In a study of Gruber et al., AH values of 9.4 (SD = 3.4) were observed in subjects without diagnosed cuff pathology. A subacromial space narrower than 6 mm on radiographs is considered pathologic and strongly indicative for supraspinatus tendon rupture [46].

The unpaired *t*-test was used to determine the sample size with a difference of AH of 3.4 mm between groups assumed as clinically relevant, comparing AH during abduction task radiographs in patients where humerus cranialisation plays a key-role compared to AH in other subgroups of SIS patients.

Based on the standardized difference: 3.4 mm/3.4 mm = 1.0, a required power of 80% and a p-value of 0.05 for significance, the Altman's Nomogram resulted in 30 shoulders/patients per group.

In our hypothesis, we defined 4 etiological mechanisms. Based on clinical experience and literature, we assume around 30% type III acromion responsible for complaints of SIS,[16] 20-30% of the SIS symptoms are caused by humerus cranialisation and pathologic motion patterns,[47] 15-20% by subacromial inflammatory processes without subacromial narrowing and 5-10% by other impinging structures than the acromion, leaving around 10-30% for a group in which SIS symptoms seem to be caused by two or more hypothesized etiologic mechanisms. With 30 patients needed in the humerus cranialisation subgroup (i.e. 30% of the patients), this leads to a total group size of 100 patients diagnosed with SIS based on patient history, physical examination, radiographs and MRI arthrography.

Additionally, we expect that around at least 25 patients will be diagnosed with another diagnosis than SIS after MRI-arthrography and radiographs [40,48]. These patients can not be included in the SISTIM study but selected patients will be analyzed separately in distinct research projects, if eligible (trial registry numbers:NTR1545 and NTR2282).

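### The 3.4 mm AH difference used for sizing has no stated support in eligible SIS patients, and 30 per group gives 97% power for it, not 80%

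*Protocol article*

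**What the plan says.** The Sample size section chooses AH as the sizing parameter and cites one study for its distribution: "AH values of 9.4 (SD = 3.4) were observed in subjects without diagnosed cuff pathology". It then gives a threshold: "A subacromial space narrower than 6 mm on radiographs is considered pathologic and strongly indicative for supraspinatus tendon rupture". An unpaired t-test is applied to a "difference of AH of 3.4 mm between groups assumed as clinically relevant". The groups compared are the patients in whom cranialisation dominates and the other SIS subgroups, with AH measured on abduction-task radiographs.

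The standardized difference is 3.4/3.4 = 1.0. With "a required power of 80% and a p-value of 0.05 for significance", a nomogram is reported to give 30 per group. Sidedness is not stated. The cranialisation subgroup is first put at 20-30% of patients. The upper figure is then used to turn 30 patients into a total of 100.

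The Selection of participants section lists "complete (full thickness) rotator cuff rupture" among the exclusions.

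**The concern.** There are two separate problems.

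**Source of the difference.** One anchor comes from people who are not studied, and the other is a limit linked to a lesion that, in its complete form, is excluded. The planned comparison lies between two sets of SIS patients, and the section gives no AH figure for either. Calling 3.4 mm clinically relevant does not show that it is a plausible gap between these subgroups.

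**Power figure.** The stated combination of 3.4 mm, 80% power and 30 per group is not consistent with itself. The total of 100 is built on that 30. As written, the paragraph does not tell a reader what the cohort can detect.

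**Working it through.** **Inputs (Sample size section):** difference 3.4 mm; SD 3.4 mm; alpha 0.05; power 80%; stated result 30 per group; total 100; cranialisation share 20-30%. A two-sided test is my assumption.

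**1. Where 3.4 mm could come from.** 9.4 - 6.0 = 3.4 mm. It is also exactly one SD. The text does not say which was meant, so either origin is an inference.

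**2. Reproducing the stated size.** Normal approximation:

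n per group = 2(z₀.₉₇₅ + z₀.₈₀)²/d² = 2(1.960 + 0.842)²/1.0² = 15.7, so 16.

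The noncentral t gives 16.7, so 17 per group. Variants by the normal approximation:

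| Variant (d = 1.0) | n per group |
|---|---|
| one-sided 0.05, 80% power | 13 |
| two-sided 0.05, 90% power | 22 |
| two-sided 0.05, 95% power | 26 |
| two-sided 0.01, 80% power | 24 |

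None gives 30. Two groups of 16 make 32 in all, so a total may have been read as a per-group number, but the article does not settle this.

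**3. Power for 3.4 mm at the planned sizes** (noncentral t, two-sided 0.05): 97% at 30 v 30, 99.5% at 30 v 70, 98% at 20 v 80.

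**4. Detectable difference at 80% power.** Approximately d = (1.960 + 0.842) × √(1/n₁ + 1/n₂). The exact d from the noncentral t is multiplied by 3.4 mm:

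| Groups | d, approximate | d, exact | mm (exact d × 3.4) |
|---|---|---|---|
| 30 v 30 | 0.723 | 0.736 | 2.5 |
| 30 v 70 | 0.611 | 0.617 | 2.1 |
| 20 v 80 | 0.700 | 0.707 | 2.4 |

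The 30 v 70 and 20 v 80 splits follow from 100 patients at the two ends of the 20-30% share, with all other patients as comparators.

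**5. Below those values.** The article gives no AH difference between SIS subgroups, so these effects are illustrative assumptions only. Power at 30 v 30, 30 v 70 and 20 v 80 is 61%, 76% and 64% for 2.0 mm, and 20%, 27% and 21% for 1.0 mm.

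**The case against.** The best defence is that a study may be sized on a difference judged relevant without claiming it is the expected one, and that the article never says 3.4 mm was obtained by subtracting 6 from 9.4. Both statements are correct, so the origin can only be described as unstated.

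A reader might go further and infer that eligible patients could hardly show 3.4 mm, because a cranialisation mean near 6 mm would imply the ruptures that are excluded. The article does not support that, for four reasons:

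- The 6 mm limit is described as a strong indicator of rupture, not as exclusive to it. If AH is normal with mean 9.4 and SD 3.4, P(AH < 6) = Φ(-1) = 16% even without known cuff disease.
- Some partial tears remain in the study and are graded on MRI (Basic MRI outcomes).
- AH is compared under an active abduction load, and the 2D radiographical section reports increased narrowing in abduction with cuff degradation.
- The cranialisation subgroup is characterised partly by low AH (scenario 1 of the section relating outcomes to mechanisms), which widens the contrast by construction. As an illustration under my own assumptions, suppose AH is normal and the lowest 30% are selected on a measure correlated r with task AH. The expected gap is then 1.66r SD, and r of about 0.6 gives roughly 3.4 mm.

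It is also not established that comparators as a whole have low AH. Subgroup 2b carries the statically reduced label, yet no clear AH decrease is expected in it.

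This defence leaves two things standing. No figure from SIS patients without full-thickness rupture supports 3.4 mm, and the power arithmetic is wrong whatever the origin of that figure.

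**Conclusion.** The concern holds in two limited parts. First, the 3.4 mm difference is unsupported for the population to be enrolled; it is not shown to be unattainable. Second, the size statement is wrong. The stated inputs need about 17 per group, and 30 per group gives 97% power for 3.4 mm. With 100 patients the AH comparison keeps 80% power down to 2.1 mm (30 v 70) or 2.4 mm (20 v 80), and a 30 v 30 comparison does so down to 2.5 mm. These figures assume SD 3.4 mm in both groups, a two-sided 0.05 level and an unpaired t-test.

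Three further inferences are not supported:

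- That the study was not sized for any realistic difference. It has 80% power for differences well below 3.4 mm, and the article gives no figure to show that the true gap is smaller still.
- That a non-significant AH result would be held against the cranialisation mechanism. Nothing in the article says so; the primary goal is classification, using many measures together.
- That the SD of 3.4 is mistaken. A 16% tail below 6 mm does not contradict the text, and the cited source is not at hand.

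Nor does the arithmetic show that 100 patients are too many, since that would rest on the same unsupported 3.4 mm.

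**What to change.** Keep the 100 patients and rewrite the sizing paragraph:

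- Remove the claim that 3.4 mm at 80% power leads to 30 per group.
- State instead that, at SD 3.4 mm and two-sided 0.05, the planned cohort has 80% power for an AH difference of 2.1 mm (30 v 70) or 2.4 mm (20 v 80), and 2.5 mm if 30 are compared with 30.
- State that 3.4 mm is not an expected difference between SIS subgroups without full-thickness rupture.
- State that differences smaller than those listed are not adequately powered.

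The cost is one paragraph, with no added patients and no new measurements. The detectable differences are smaller than the 3.4 mm now claimed, so the corrected statement does not weaken the case for the cohort.

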#### Relate outcome measures to pathophysiological mechanisms

Results of the recorded clinical, radiological and biomechanical measurements will be interpreted and combined in order to classify patients in to the hypothesized etiological subgroups (Figure 4). Ultimately, if a patient has evidence of co-activation of arm depressors with abduction but no signs of shape parameters (e.g. acromion classification) playing a role, this would implicate that an intrinsic and dynamic mechanism is the main pathologic mechanism. On the other hand, evidence of e.g. a type III acromion (hooked) without any signs of relative cranial translation of the humerus would be suggestive of a primarily extrinsic and static/structural cause.

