**Figure 4 F4:**
[figure not shown]
**Schematic outline for relating outcome measures to pathophysiological mechanisms**. We expect to identify one or more of the hypothesized etiological mechanisms in each SIS patient. These mechanisms might be related to the reported variations in SIS symptoms, course, and treatment outcome. (MRI = Magnetic Resonance Imaging, X-ray & EMG task = radiographs during EMG recorded abduction and adduction tasks for measurements of acromiohumeral distance, and FoB = 3D kinematics with Flock of Birds system).

The following scenarios are considered:

1) Dynamically reduced subacromial space, due to (relative) cranial translation of the humerus.

Humerus cranialisation causing encroachment of subacromial tissues will be characterized by limited AH in resting state on standard radiographs, further decrease in AH during abduction tasks, and decreased reconstructed subacromial volume (MRI). In some patients, this cranialisation might be (partially) compensated by I) co-activation of arm adductor muscles, and/or II) altered kinematics of the humerus and the scapula (scapulohumoral rhythm). Nevertheless, instead of a compensation mechanism, altered scapulohumeral rhythm can also be a cause of SIS in some patients (e.g. decreased scapula lateral rotation during arm abduction, with consequent relative cranial translation of the humerus). Pain is suspected to be the main trigger for compensation mechanisms. Therefore, we expect that these compensation mechanisms will be less manifest during the second round of experiments, after a subacromial injection with lidocaine.

Particularly relevant positive outcome measures for this subgroup are: decreased AH, low AR (adductor co-activation), altered Principal Action for adductor muscles, decreased reconstructed subacromial volume during active abduction, degeneration of rotator cuff muscles and altered scapulohumeral rhythm.

2a) Statically reduced subacromial space, due to structural narrowing (classic etiology). The subacromial space can be narrowed as a consequence of structural anatomic variations, e.g. a hooked acromion impinging on the subacromial tissues. These potential causes will be investigated and quantified using shoulder radiographs and (segmented) MRI-arthrographies.

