As a consequence of structures impinging on the rotator cuff, compensation mechanisms might be present to prevent further subacromial encroachment, including altered scapulohumeral rhythm (increased lateral rotation or increased posterior tilt during arm abduction) and adductor co-activation during arm abduction. Again, we expect that these compensations mechanisms will be less manifest after a subacromial injection with lidocaine.

Important outcome measures for this subgroup are: shape parameters of scapula (hooked acromion, Bigliani classification, acromial spurs) and humerus, the presence and extend of rotator cuff tendinosis (fibrosis, tendinitis, partial articular or bursal side tear).

2b) Statically reduced subacromial space, as a consequence of subacromial inflammatory processes, without signs of actual structural subacromial narrowing.

In some subjects, symptoms of SIS are related to predominantly intrinsic causes. In these patients, we expect to find little or no anatomic variations impinging on the cuff and no evidently decreased AH. The hypothesized disbalance between subacromial volume and the space needed for subacromial structures can be caused by e.g. subacromial oedema, fibrosis, tendinosis and tendinitis, which will be mainly assessed by means of MRI.

As a consequence of the subacromial inflammatory reaction and pain, patients might have an altered scapulohumeral rhythm and adductor co-activation.

Main outcome measures for characterizing this subgroup are: the presence and extend of rotator cuff tendinosis (fibrosis, tendinitis, partial articular or bursal side tear) and subacromial oedema.

2c) Statically reduced subacromial space due to encroachment of subacromial tissues by an adjoining pathology or other structures than the acromion.

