#### Statistical analyses

Patient data, including patient characteristics, physical examination, interview, radiological findings, questionnaires, psychological scores, biomechanical measurements and MRI findings will be entered in a database.

With regards to presence of cranial translation of the humerus as detected on radiographs during rest and abduction and adduction tasks, statistical analysis will be performed by a means of repeated measures ANOVA, with the measure of co-contraction controlled as a confounding factor.

For the isometric Principal Action EMG measurements, data are tested by means of a General Linear Model analysis for repeated measures, controlling for factors Muscle, subacromial anaesthetics, sAH and VAS for pain.

RoM in standardized motions will be analyzed with a General Linear Model analysis for repeated measures, controlling for factors VAS pain, subacromial anaesthetic, dAH and sAH. dAH obtained from 3D-kinematics will be analyzed equally.

Additionally, we will use students' unpaired t-tests to compare continuous variables (e.g. patient characteristics, clinical scores, RoM, dAH) between defined pathologic subgroups.

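### Acromiohumeral distance helps define the cranialisation subgroup and is also the variable whose between-subgroup t-test sizes the study, so the stated alpha and power do not apply to that test

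*Protocol article*

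**What the plan says.** **The sizing comparison.** The Sample size section uses an unpaired t-test, "comparing AH during abduction task radiographs in patients where humerus cranialisation plays a key-role compared to AH in other subgroups of SIS patients". Its inputs are a difference of 3.4 mm, an SD of 3.4 mm, 80% power and a significance level of 0.05. It arrives at 30 patients per group. Because the cranialisation subgroup is taken to be 30% of patients, the total is 100.

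**How subgroups are formed.** Under Relate outcome measures to pathophysiological mechanisms, the study's own clinical, radiological and biomechanical results "will be interpreted and combined in order to classify patients in to the hypothesized etiological subgroups". Scenario 1, cranialisation, "will be characterized by limited AH in resting state on standard radiographs, further decrease in AH during abduction tasks", together with a decreased reconstructed subacromial volume. Decreased AH comes first in a list of six relevant measures. The others are low activation ratio, altered principal action, decreased reconstructed volume, cuff muscle degeneration and altered scapulohumeral rhythm.

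**The comparators.** A hooked acromion "without any signs of relative cranial translation of the humerus would be suggestive of a primarily extrinsic and static/structural cause". For the inflammatory subgroup (2b) the authors expect "little or no anatomic variations impinging on the cuff and no evidently decreased AH".

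**The analysis.** The Statistical analyses section says "we will use students' unpaired t-tests to compare continuous variables (e.g. patient characteristics, clinical scores, RoM, dAH) between defined pathologic subgroups". It describes dAH as obtained from 3D kinematics. Radiographic cranial translation across rest, abduction and adduction is analysed by repeated measures ANOVA.

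**The concern.** A two-sample t-test has its nominal error rate only if group membership is unrelated to the outcome under the null hypothesis. Here membership depends partly on the outcome: low AH during the abduction task moves a patient towards the cranialisation subgroup. The comparators are described partly by the opposite finding. The two groups will then differ in AH because of the sorting, whether or not separate mechanisms exist.

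The primary goal is to identify and classify distinct mechanisms. A significant AH difference between the resulting subgroups could easily be read as support for that classification, although much or all of it may come from the assignment rule. The sample size has the same weakness, since its significance level and power describe a comparison of groups formed independently of AH.

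**Working it through.** **1. The plan's own figure.** With a standardised difference of 3.4/3.4 = 1.0, two-sided 0.05 (sidedness is not stated) and 80% power, n per group = 2 × (1.96 + 0.84)² / 1.0² = 15.7, so 16, or 17 by the exact t-test. The stated 30 per group does not reproduce. It is close to the total for both groups (32 to 34). This is a separate matter, and correcting it would not remove the problem described here.

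**2. Is the same variable on both sides?**
- Sizing test: AH on abduction-task radiographs, cranialisation subgroup against the others.
- Scenario 1: limited resting AH and a further fall in AH during abduction tasks.
- No passage says that classification is made without AH, blind to AH or in a separate sample.

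The overlap is literal for radiographic AH. For dAH it is indirect. dAH is reconstructed from motion tracking and MRI bone shapes, as is the dynamic subacromial volume listed for scenario 1. It is closely related to the classifiers but is not itself named as one.

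**3. Difference produced by selection alone.** Assume one normal AH population (mean 9.4, SD 3.4 mm, from the Sample size section) with no subgroups, and label the 30% with the most cranialised classification score. Let ρ be the correlation between that score and task AH. The expected difference is

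ρ × SD × [φ(z)/p + φ(z)/(1−p)], with p = 0.30, z = −0.524, φ(z) = 0.3477.

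The bracket is 0.3477/0.30 + 0.3477/0.70 = 1.159 + 0.497 = 1.656. At ρ = 1 this gives 1.656 × 3.4 = 5.6 mm; at ρ = 0.5 it gives 2.8 mm. The plan calls 3.4 mm clinically relevant.

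**4. False-positive rate.** Simulation of the same setting: 100 patients, lowest 30 on the score labelled, unpaired two-sided t-test on task AH at 0.05, 5,000 studies per row.

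| ρ (assumed) | Mean difference (mm) | Significant |
|---|---|---|
| 0 | 0.0 | 5.5% |
| 0.2 | 1.1 | 32% |
| 0.3 | 1.7 | 64% |
| 0.41 | 2.3 | 90% |
| 0.5 | 2.8 | 98% |
| 0.7 | 3.9 | 100% |
| 1.0 | 5.6 | 100% |

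Repeat runs moved these rates by about one percentage point. The rates do not depend on the mean and SD used. If 20 patients are labelled (the lower end of the plan's 20–30%), the rates are 29%, 57%, 85% and 96% at ρ = 0.2, 0.3, 0.41 and 0.5.

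**5. Locating ρ.** The article gives no weights. If task AH were one of six equally weighted, mutually independent criteria, ρ would be 1/√6 = 0.41, and the simulated rate is 89%. This is an illustration, not the plan's rule.

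**6. An alternative basis for 100 patients.** The 95% half-width for a subgroup proportion is 1.96 × √(0.3 × 0.7/100) = 0.090 at 30% and 1.96 × √(0.2 × 0.8/100) = 0.078 at 20%.

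**The case against.** The strongest reply is that this is a descriptive study and that the t-test serves only to determine the sample size. AH was chosen as a recognised parameter while most of the other techniques are new. The radiographic AH analysis that is actually described is a repeated measures ANOVA over tasks. The subgroup t-tests name dAH, which is a different measurement. AH is one of six measures combined without a stated cut-off or weight. The text also allows cranialisation to be partly compensated, and patients with combined mechanisms may fall among the comparators with low AH too.

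Much of this stands, and it limits what may be concluded. A reader might infer four stronger things that the article does not support:
- **That significance is practically certain.** This needs a rule close to ranking patients on AH and labelling the lowest 30. No such rule is stated, and at a weak correlation the rate is about a third.
- **That the diagnostic and treatment flowcharts would rest on an AH p-value.** No passage says so; they are to follow from the classification.
- **That dAH is itself a stated classifier.** It is not listed as one.
- **That subgroup 2b is defined by AH.** The absence of an evident AH decrease is an expectation there. Its listed characterising measures are tendinosis and oedema.

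The reply does not remove the overlap. The article itself chose a hypothesis test with a significance level and power as the basis for 100 patients, on a variable that it also uses to characterise one of the two groups. An operational classification rule may well sit in a fuller document. Even so, the comparison becomes valid only if AH is removed either from the rule or from the test.

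**Conclusion.** The point holds in a limited form. Task AH is both a defining feature of the cranialisation subgroup and the variable of the sizing test, so the stated 5% level and 80% power do not describe that test. With no true subgroups and 30 of 100 patients labelled, the false-positive rate runs from about 32% to 98% for assumed correlations of 0.2 to 0.5, and returns to about 5% only if the classification is unrelated to AH. These rates rest on normality, on a fixed number of labelled patients and on a correlation that the article does not give. The direction is certain if AH is used in classifying; the exact size is not.

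A significant difference in AH between subgroups is therefore not evidence of distinct mechanisms. The same caution applies to dAH to the extent that it tracks the classifiers. The classification itself, the measurements and the figure of 100 patients are not shown to be wrong by this point.

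**What to change.** 1. State that AH, dAH, reconstructed subacromial volume and any other variable used to assign subgroups are reported by subgroup as estimates, with no p-value taken as confirmation of the subgroups.
2. Limit between-subgroup tests to variables outside the assignment rule, for example DASH, WORC, Constant score, SF-36, IPQ and VAS pain.
3. Restate the justification for 100 patients without the AH t-test. One option is the precision of subgroup proportions: a 95% half-width of about 9 points at 30% and 8 points at 20%.

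The cost is wording in the Sample size and Statistical analyses sections; no measurement or recruitment step changes. The downside is that an AH p-value can no longer be offered as confirmation of the subgroups.

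### The 30 patients per group do not follow from the stated inputs: a standardised difference of 1.0 at 80% power needs 17 per group, and the total of 100 is built on the 30

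*Protocol article*

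**What the plan says.** The Sample size section of the protocol article bases the calculation on AH. The unpaired t-"test was used to determine the sample size with a difference of AH of 3.4 mm between groups assumed as clinically relevant", and the comparison is of AH on abduction-task radiographs between the humerus-cranialisation subgroup and other subgroups of SIS patients. The SD comes from a cited study in which "AH values of 9.4 (SD = 3.4) were observed in subjects without diagnosed cuff pathology".

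The calculation itself reads: "Based on the standardized difference: 3.4 mm/3.4 mm = 1.0, a required power of 80% and a p-value of 0.05 for significance", after which "the Altman's Nomogram resulted in 30 shoulders/patients per group".

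The section then treats 30 as the number needed in the cranialisation subgroup alone. It takes that subgroup to be 30% of patients, the upper end of its own 20-30% range, and arrives at 100 patients. No other derivation of the 100 is given.

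**The concern.** A standardised difference of 1.0 is large, and 30 per group is well above what it usually calls for at 80% power. All the inputs are printed beside the result, so the figure can be checked directly. This is not a detail that a condensed article leaves to the full protocol or to an analysis plan: the stated inputs and the stated result disagree.

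The stake is the justification of the enrolment target. The 30 is carried straight into the 100. If it is wrong, the stated power is wrong, and so is the reason given for the number of patients who undergo the research procedures, chiefly the task radiographs with EMG and the force tasks repeated after lidocaine.

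**Working it through.** **Inputs, all from the Sample size section**

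- Test: unpaired t-test on AH.
- Difference: 3.4 mm. SD: 3.4 mm. Standardised difference d = 3.4 / 3.4 = 1.0.
- Power 80%, significance level 0.05. Sidedness is not stated. Two-sided is assumed; one-sided is also tried below.
- Equal groups, as the per-group wording implies.

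**Step 1. Try to reproduce 30 per group**

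Normal approximation: n per group = 2 × (1.96 + 0.84)² / d² = 2 × 7.85 / 1.0 = 15.7, so 16.

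Exact t-test: power comes from the noncentral t distribution with n1 + n2 − 2 degrees of freedom and noncentrality d / √(1/n1 + 1/n2).

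| Per group | Power at d = 1.0 |
|---|---|
| 15 | 75.3% |
| 16 | 78.1% |
| 17 | 80.7% |
| 30 | 96.8% |

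The requirement is 17 per group. The stated 30 is 30 / 17 = 1.8 times that and is not reproduced. With 30 per group, the difference detectable at 80% power is 0.74 SD, or 2.5 mm, not 3.4 mm.

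**Step 2. Look for a variant that gives 30**

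| Variant | Per group |
|---|---|
| One-sided 0.05, 80% power | 13 to 14 |
| 7:3 allocation | 12 in the smaller group |
| Inflation for a rank test | 18 to 20 |
| Bonferroni for 3, 4 or 6 comparisons | 23, 24 or 27 |
| Bonferroni for 10 comparisons | 29 |
| 97% power | 30 to 31 |
| Two-sided 0.01, 90% power | 30 to 32 |
| Dropout needed to go from 17 to 30 | 1 − 17/30 = 43% |

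Only the last four come near 30. The article states none of them, and two contradict the power or significance level that it does state.

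**Step 3. Follow the figure into the total**

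- As stated: 30 / 0.30 = 100.
- With 17 at 30% prevalence: 17 / 0.30 = 56.7, so 57.
- With 17 at 20% prevalence: 17 / 0.20 = 85.

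Both corrected totals lie below 100.

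**Step 4. What 100 patients deliver**

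The section does not say whether the other subgroups are pooled or taken one at a time. The Statistical analyses section plans unpaired t-tests between defined subgroups, so both readings are shown. The small group sizes follow from the article's own shares: 15-20% inflammatory and 5-10% other impinging structures, of 100 patients.

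| Comparison | Power for 3.4 mm | Difference at 80% power |
|---|---|---|
| Pooled, 30 v 70 | 99.5% | 0.62 SD, about 2.1 mm |
| Pooled, 20 v 80 | 97.7% | 0.71 SD, about 2.4 mm |
| Pairwise, 30 v 15 | 87% | about 3.1 mm |
| Pairwise, 30 v 10 | 76% | about 3.6 mm |
| Pairwise, 30 v 5 | 52% | about 4.7 mm |

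Every row uses an SD of 3.4 mm, which was observed in people without diagnosed cuff pathology. That it holds for SIS patients is an assumption.

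**The case against.** The strongest reply is that the error is conservative. The article asks for 80% power, and 30 per group exceeds it. The total of 100 covers the corrected requirement at both ends of the prevalence range (57 and 85). The primary goal is to identify and classify mechanisms in a descriptive study, not to run this one t-test, and no analysis or eligibility rule depends on the figure. All of this stands, and it lowers the severity. It does not make the stated number right, and the article offers no other reason for 100.

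The burden argument also has limits. MRI-arthrography belongs to the eligibility work-up and is read locally for clinical purposes, and a positive lidocaine test is itself a selection criterion. Only the task radiographs and the experimental session with lidocaine are clearly procedures that a smaller total would spare.

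A reader might infer that 30 is the total for both groups, mistaken for the size of one. The documents do not support this. The total is 32 by the normal approximation (31.4 before rounding) and 34 by the exact test, and 15 per group reaches only 75.3% power. The nomogram reading is not shown, so the origin of the 30 stays unknown.

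**Conclusion.** The point holds as an arithmetic error of moderate severity. At d = 1.0, two-sided 0.05 and 80% power, the requirement is 17 per group, not 30; the stated 30 has 96.8% power. One-sided testing would only widen the gap. The figure carries into the 100, which is more than this calculation requires: 57 at 30% prevalence, 85 at 20%.

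Two stronger readings should be resisted. One is that the study should enrol far fewer patients. That would require all other patients to be pooled into one comparison group, which the article does not say, and it would ignore the planned comparisons between subgroups, some of which have limited power even with 100 patients. The other is that the error leaves the AH comparison underpowered. It does the opposite: in the pooled comparison power is at least 97.7% across the stated prevalence range. The low power of pairwise tests against the smallest subgroups comes from their expected size, not from this error.

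The results rest on the article's own inputs, on two-sided testing, and on the 3.4 mm SD carrying over to SIS patients.

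**What to change.** In the Sample size section:

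1. Replace 30 per group with 17 per group for 80% power at a standardised difference of 1.0 (two-sided 0.05, unpaired t-test), and state the sidedness.
2. Stop presenting 30 as the number needed for 80% power, both in the nomogram sentence and where the total is derived.
3. If 100 is kept, say that it exceeds what this calculation requires and state what it delivers, with conditions. Pooled: 99.5% power for 3.4 mm at 30 v 70 (80% power for about 2.1 mm), and 97.7% at 20 v 80 (80% power for about 2.4 mm). Pairwise: about 87%, 76% and 52% for 3.4 mm at 30 v 15, 30 v 10 and 30 v 5.
4. Say which of the two comparisons is meant, and that all figures assume an SD of 3.4 mm in SIS patients.

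The cost is a change of text. No patients, visits or measurements are added.
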